### Intervention group

All interventions received by the intervention group were carried out in a separate activity room with an area of 20 m^3^ to ensure no interference. The activity room will be equipped with seats approximately, drinking water, and other necessary items. Moreover, necessary first-aid items will be also provided to ensure patient safety. The research team will provide materials and related things for ACT. Throughout the intervention, the health care workers will keep the patient safe at all times.

For the intervention group, group-based acceptance and commitment therapy intervention will be given for 8 weeks in addition to TAU, which will be completed by 2 graduate students, both of whom were systematically trained group-based ACT consultants, and will also lead the group consultation activities. Each group-based ACT intervention will consist of 10 ~ 12 people, once a week for 40 to 60 min, for 8 consecutive weeks. The content consists of eight sessions: confronting the agenda, accepting everything, objectively observing cognition, the hours, feeling yourself, identifying your value, looking forward, and review. The specific intervention content of each module is shown in Table 1.

**Table 1 Tab1:** An overview of the group-based ACT program for older stroke survivors

Session	Content
Confronting the Agenda	Start with an “Ice-breaking tour” (5–10 min) Patient self-introduction (10–15 min) Introduction of ACT team members and content (5 min) Mindfulness exercises (10–15 min) Home task (5 min)
Accepting everything (Acceptance)	Begin with a mindfulness exercise and homework review (5–10 min); Watch a video of sinking into a swamp (10-15 min); Play the game “Chinese Finger Glove” (10–15 min); Share and summarize (10–15 min); Home task (5 min).
Observing cognition objectively (Cognitive Defusion)	Homework review (5–10 min); Play the video “Passengers on the Bus” (5–10 min); Play the game “Folder push” (10 to 15 min); Share and summarize (10–15 min); Home task (5 min).
The Hours (Being Present)	Begin with a review of last week’s homework (5-10 min); Mindful eating (10 min); Mindful breathing exercise (10-15 min); Share and summarize this activity (5–10 min); Home task (5 min).
Feeling yourself (Self as Context)	Begin with a mindfulness exercise and homework review (5-10 min); Play the video “Sky and Weather” (5 min); Share and summarize (15-20 min); Share poems, stories or elements of Chinese culture with the patients (5–10 min); Home task (5 min).
Identifying your value (Values)	Start with a few people sharing thoughts on last week’s homework (5–10 min); Play the game “Life Button” (15-20 min); Share and summarize (5-10 min); Home task (5 min).
Looking forward (Committed Action)	Start with a few people sharing thoughts on last week’s homework(10-15 min); Set goals (20–25 min); Share and summarize (5–10 min); Home task (5 min).
Review	Start with homework review (5 min); Play photos and videos (5–10 min); Share feelings (15-20 min); Give blessings, encouragement, and gifts (10–15 min).

### Blinding

The researcher conducting baseline assessments (T0) will be blinded to participant treatment allocation, as participants will also be blinded to randomization after the baseline assessment (T0). It is not possible for the treating psychologists providing the intervention to be blinded. However, an independent assessor who will join to complete the post-treatment (T1) and one-month follow up assessment (T2), will be blinded to the condition. The success of blinding will be assessed by having independent assessors (i) indicate which condition they thought the participant will be randomly assigned to and (ii) indicate whether the participant will disclose their treatment condition or not. Data analysis will be undertaken by a graduate student with no direct contact with the individual research group to remain blinded to the treatment conditions. It is expected that unblinding will be not needed for independent assessors or statisticians, therefore in this study, unblinding is not permissible.

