**Methods and analysis:**

This study is a randomized, single-blind, wait-list controlled, parallel-arm trial. A total of 66 stroke survivors will be randomly assigned to wait-list control group or intervention group. Participants in wait-list control group will receive treatment as usual (TAU), while the intervention group will receive group-based ACT once a week for eight weeks. The primary outcome measure being EA, and the secondary outcome measures being PSD, psychological distress, and quality of life. Results of the two groups will be blindly assessed by professional evaluators at baseline (T0), post-treatment (T1), and one-month follow up (T2).

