### Study design

This study is a randomized, single-blind, wait-list controlled, parallel-arm trial. Older stroke survivors will be selected from a tertiary hospital in China using convenience sampling between December 2022 to March 2023. Older stroke survivors who meet the inclusion criteria will be informed of the purpose and methods of the study and sign the informed consent forms through face-to-face communication. Then, they will be randomly assigned to either a wait-list control group (TAU group) or an intervention group (group-based ACT group). EA, PSD, psychological distress and quality of life of patients will be blindly evaluated at baseline (T0), post-treatment (T1), one-month follow up (T2) for both groups (see Fig. 1).

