### Quality Control

The therapist will post reminders and trailers in the WeChat group before each intervention in ACT group.The therapist will summarize and comment on the day after each session.The therapist will clock in the WeChat group to supervise the completion of the homework of the patients, and provide comments and feedback to the patients who actively share the experience after the completion of the homework. Patients can also communicate with each other in the WeChat group.Considering the declining vision and cognitive ability of the older population, large-sized intervention explanatory sheets will be distributed in this study, and each patient will be provided with a helper to understand the intervention content.If required, the measures can be read out to the participant by the assessor to assist with understanding, and a separate sheet with the measure’s Likert response scales will be provided to the participant in a larger font to compensate for visual, attention/cognitive, and reading impairments in the older adults.We will compensate for the time and effort the study participants put into the study. In the wait-list control group, we will help them understand the disease knowledge, distribute the recommended recipe list of stroke survivors, the prevention manual of recurrent stroke, answer questions at any time and so on. The intervention group will receive these equal compensations, and all the patients will be encouraged to complete the intervention by compensating them with daily necessities, such as tissues, masks, and swabs, before each week of the intervention. Of course, the wait-list control group will also have equal compensation when the formal intervention ended.

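### The stated blinding does not hold for the primary outcome: participants know their arm once treatment starts, and they supply the AAQ-II answers

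*Protocol article*

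**What the plan says.** The protocol article makes four statements about blinding.

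- **Design label (Study design):** "This study is a randomized, single-blind, wait-list controlled, parallel-arm trial". The blinded party is not named there.
- **Outcome assessment:** the abstract says "Results of the two groups will be blindly assessed by professional evaluators" at T0, T1 and T2. Study design goes further and lists the outcomes: "EA, PSD, psychological distress and quality of life of patients will be blindly evaluated". That list includes the primary outcome, experiential avoidance (EA).
- **Participants (Blinding):** the baseline researcher is said to be blinded, "as participants will also be blinded to randomization after the baseline assessment (T0".
- **Assessor and analyst (Blinding):** "an independent assessor who will join to complete the post-treatment (T1) and one-month follow up assessment (T2), will be blinded to the condition". The data analyst is also to be kept unaware of the treatment conditions. As a check on blinding, assessors guess the allocation and "indicate whether the participant will disclose their treatment condition or not".

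On how the scales are completed, Quality Control says that the assessor may read the measures out where needed and that "a separate sheet with the measure’s Likert response scales will be provided to the participant in a larger font".

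**The concern.** Two properties are claimed that the design does not appear to have: that participants are blind to their arm after baseline, and that the primary outcome is evaluated blind. If the person who answers the primary questionnaire knows the arm, a blinded assessor who hands over or reads out that questionnaire does not make the answer blind.

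What is at stake is the interpretation of the main result. The comparator is a waiting list. Expectation of benefit in the ACT arm and disappointment in the waiting arm would plausibly both move self-reports towards the study hypothesis. The Discussion also describes improving EA as the core purpose of the therapy, so the primary scale asks about what the sessions teach. A reader told that EA was blindly evaluated would discount this possibility when they should not.

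**Working it through.** No stated figure is in dispute, so the check is a comparison of sections, followed by one illustration.

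**Step 1. Do participants know their arm after T0?**

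| Section | What participants experience |
|---|---|
| Study design | The study's purpose and methods are explained before consent, which precedes randomisation. |
| Intervention group and Table 1 | Eight weekly ACT sessions in groups of 10 to 12. The first session presents the ACT team and content, and all but the last set home tasks. |
| Quality Control | ACT participants have a therapist-run WeChat group with session reminders and homework feedback. |
| Wait-list control group | Usual care for eight weeks in a room away from the ACT site, with ACT afterwards. |
| Blinding | Assessors record whether the participant disclosed the condition, which presupposes that the participant knows it. |

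A patient who has been told what the trial compares, and who then either attends ACT groups or waits for them, knows the allocation. The participant-blinding clause conflicts with all of these sections, including its own.

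**Step 2. Who produces the primary outcome?** Primary outcome measures describes a seven-item and a ten-item AAQ-II. Both are Likert questionnaires, so the point does not depend on which is used. Quality Control gives the participant the response sheet and has the assessor read items aloud if required. The answers are therefore the participant's. The article never uses the term self-report for the AAQ-II; this is an inference from format and administration, and a firm one.

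**Step 3. What does the existing blinding cover?** A blinded T1/T2 assessor cannot favour an arm when presenting or scoring the items, and a blinded analyst cannot favour one in the analysis. Neither affects how an unblinded participant chooses to answer.

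**Step 4. Size.** The document gives nothing from which a bias could be estimated. To show sensitivity only, suppose no true effect and a difference in reporting of b SD between arms. For n per arm and a two-sided 5% z-test:

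P(reject) = 1 − Φ(1.96 − λ) + Φ(−1.96 − λ), with λ = b / √(2/n).

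Example: b = 0.2 and n = 33 give λ = 0.2 × √16.5 = 0.81 and P = about 0.128.

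| Assumed bias b (SD) | n = 33 per arm (planned) | n = 25 per arm (before the 30% expansion) |
|---|---|---|
| 0.1 | 0.069 | 0.064 |
| 0.2 | 0.128 | 0.109 |
| 0.3 | 0.230 | 0.186 |
| 0.4 | 0.369 | 0.293 |
| 0.5 | 0.528 | 0.424 |

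The sample sizes come from Sample size calculation. Every value of b is an assumption.

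**The case against.** **The clause may be a slip of language.** It is given as the reason why the baseline researcher is blind, which makes best sense if allocation is unknown until T0 is finished. That may well be what was meant, and the disclosure check fits it. It is not what is written, however, and this reading leaves untouched the claim in Study design that EA is evaluated blind.

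**Single-blind can mean assessor-blind, and unblinded participants are normal in psychotherapy trials.** Both points stand. The design is not at fault; the description is. The abstract's sentence, which speaks of evaluators, needs only a definition. The Study design sentence, which extends blindness to the outcomes themselves, needs correcting.

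**Three stronger readings are tempting but not supported.**

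- A reader might infer that the main result is simply unblinded. That goes too far: the T1/T2 assessor and the analyst are blinded, and this protects real steps.
- A reader might infer that the HAM-D alone is a blinded rating and can anchor the interpretation. The article does not say who rates it. Secondary outcome measures describes its scoring as a Likert method too, and Eligibility criteria speaks of patients reporting distress at a HAM-D threshold.
- A reader might want the comparison repeated without patients who disclosed their arm. Disclosure happens after randomisation and may well differ by arm, since ACT attendees have sessions to mention. The remaining subset would not be a randomised comparison, would depart from the intention-to-treat basis in Statistical analysis, and would shrink a small sample.

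**Conclusion.** The concern holds in a limited form. Participants are not blind after allocation, and the participant supplies the AAQ-II answers, so the stated blinding of the primary outcome does not hold. The same applies to any other patient-answered scale. The Distress Thermometer appears to be one; for the SS-QOL and the HAM-D the article does not settle who gives the rating.

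The consequence is a limit on what an AAQ-II benefit can be said to show, not a defect in randomisation or analysis. The illustrative range of about 7% to 53% at 33 per arm rests wholly on assumed biases of 0.1 to 0.5 SD and should not be quoted as an estimate for this trial. The conclusion itself rests on one inference, that a Likert questionnaire whose response sheet is given to the participant is answered by the participant.

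**What to change.** 1. **Blinding:** replace the participant clause with a statement that allocation is concealed until T0 is complete and that participants are not blinded afterwards.
2. **Abstract and Study design:** define single-blind, and the phrases about blind assessment or evaluation, as blinding of the assessor and the analyst only.
3. **Outcome sections:** state that the AAQ-II, and any other patient-answered scale such as the Distress Thermometer, is reported by unblinded participants, and that a benefit on it will be interpreted as such. State which scales, if any, the blinded assessor rates.
4. **Blinding check:** report the assessors' allocation guesses and the disclosure data by arm, descriptively. Do not present an analysis that excludes patients who disclosed as a randomised comparison.

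The cost is some rewording and a descriptive table from data already planned. Randomisation, outcomes, sample size and the main analysis stay as they are. The downside is a weaker blinding claim.

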### Quality Control

The therapist will post reminders and trailers in the WeChat group before each intervention in ACT group.The therapist will summarize and comment on the day after each session.The therapist will clock in the WeChat group to supervise the completion of the homework of the patients, and provide comments and feedback to the patients who actively share the experience after the completion of the homework. Patients can also communicate with each other in the WeChat group.Considering the declining vision and cognitive ability of the older population, large-sized intervention explanatory sheets will be distributed in this study, and each patient will be provided with a helper to understand the intervention content.If required, the measures can be read out to the participant by the assessor to assist with understanding, and a separate sheet with the measure’s Likert response scales will be provided to the participant in a larger font to compensate for visual, attention/cognitive, and reading impairments in the older adults.We will compensate for the time and effort the study participants put into the study. In the wait-list control group, we will help them understand the disease knowledge, distribute the recommended recipe list of stroke survivors, the prevention manual of recurrent stroke, answer questions at any time and so on. The intervention group will receive these equal compensations, and all the patients will be encouraged to complete the intervention by compensating them with daily necessities, such as tissues, masks, and swabs, before each week of the intervention. Of course, the wait-list control group will also have equal compensation when the formal intervention ended.

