### Interventions

#### Wait-list control group

The wait-list control group will receive TAU treatment for eight weeks, and the intervention will take place in a separate room in the inpatient building of the supporting unit, away from the ACT intervention site. When the intervention group has completed all the ACT procedures, the wait-list control group will receive the same ACT intervention as the intervention group. The TAU intervention is as follows. (1) Disease knowledge guidance, including introducing to patients the causes of stroke, how to identify stroke, clinical manifestations, treatment methods and other knowledge, so that patients can have a more comprehensive understanding of stroke; (2) Medication guidance and health education, including the mode of medication, time of medication, precautions for medication, possible side effects after medication and how to deal with them; (3) Basic psychological guidance, including counseling, persuasion and other forms, enabling patients to feel respect and care, increase their trust in medical staff, and rebuild their confidence to resume normal life; (4) Rehabilitation guidance, including rehabilitation training timing, rehabilitation training methods and precautions; (5) Psychological nursing, including encouraging patients, timely answering their doubts in the process of rehabilitation treatment, reducing their fear of disease, and establishing their confidence in early recovery.

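### Weekly goods meant to encourage completion go to the ACT arm before T1, but to the wait-list arm only after the intervention has ended

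*Protocol article*

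**What the plan says.** The Quality Control section describes two layers of compensation.

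- **Information and support.** For the wait-list arm the team will explain the disease and "distribute the recommended recipe list of stroke survivors, the prevention manual of recurrent stroke, answer questions at any time and so on". These items are shared: "The intervention group will receive these equal compensations".
- **Goods.** The same sentence continues that "all the patients will be encouraged to complete the intervention by compensating them with daily necessities, such as tissues, masks, and swabs, before each week". The stated purpose is completion.

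The closing sentence of the section sets the timing for the other arm: "the wait-list control group will also have equal compensation when the formal intervention ended".

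On the calendar, "The wait-list control group will receive TAU treatment for eight weeks", in parallel with the eight weekly ACT sessions described under Intervention group. Study design places T0 at baseline, T1 after treatment and T2 one month later.

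**The concern.** In a wait-list trial the therapy is deferred in one arm. Everything else that can be kept equal should be, above all anything meant to keep patients in the study. Here an incentive with a declared retention purpose appears to operate in one arm only, over the T0–T1 interval on which the post-treatment comparison rests.

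Two things are at stake. First, retention up to T1 may differ between arms for a reason unrelated to ACT. Second, patients who receive goods every week may answer somewhat more favourably. The primary AAQ-II is a questionnaire answered by the patient, and the distress thermometer records the patient's own level over the past week. A blinded assessor does not remove goodwill from answers of that kind.

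**Working it through.** The protocol gives no figure for this point, so the check sets its statements side by side.

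**1. Who gets the goods weekly?** Taken alone, the clause on goods refers to all patients and could cover both arms. Two features point the other way. The clause continues a sentence whose subject is the intervention group. The next sentence then says that the wait-list arm will also have equal compensation, at a later time. If controls already received the goods each week, that sentence would have little purpose. The natural reading is that the ACT arm receives them weekly and controls later.

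**2. What differs between T0 and T1?**

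| Item | ACT arm | Wait-list arm |
|---|---|---|
| Usual treatment, eight weeks | yes | yes |
| Information items and answers to questions | yes | yes |
| Weekly goods | one per week × 8 weeks = up to 8 | 0 |

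The information items appear in both columns and cancel. The goods do not.

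**3. Are the goods part of the therapy under test?** Table 1 lists the content of all eight sessions, and the weekly goods are not in it. They appear only under Quality Control, as compensation. They are therefore an addition that coincides with arm, not a component of ACT.

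**4. When does the deferred compensation arrive?** The section says only that it follows the end of the formal intervention and does not place it relative to T1 or T2. The Wait-list control group section promises controls ACT once the intervention group has finished. Ethical considerations and dissemination makes this conditional on ACT proving effective. Goods could thus reach controls between T1 and T2 or after T2. The T1–T2 interval may also be affected, but the text does not settle this.

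**5. Does the planned analysis absorb the difference?** Statistical analysis plans an intention-to-treat generalized linear mixed model and a mixed model for repeated measures with baseline-adjusted differences. These use partial data and correct for drop-out that the observed scores explain, that is, under missing at random. They do not correct drop-out that depends on unobserved scores. Nor can they separate goodwill from treatment, because receipt of the goods coincides with arm.

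**6. Was unequal loss foreseen?** Sample size calculation expands each group by the same 30% (25 × 1.3 = 32.5, taken as 33). The planning makes no allowance for loss that differs by arm.

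**The case against.** The strongest case on the other side is that this is trivial. Tissues, masks and swabs are worth little. The ACT arm already differs by group sessions, peer contact, reminders and therapist feedback, all inherent in comparing ACT plus usual treatment with usual treatment alone. Any goodwill from the goods is probably small beside these. Controls are not without reason to stay: they receive the information items, and are promised compensation and, subject to the condition noted above, ACT. The compensation is described as being for time and effort, and the ACT arm gives more of both.

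Much of this stands, and it limits the point to a cheap improvement. It does not remove it. The larger differences belong to the treatment contrast, whereas the goods do not. Controls also give eight weeks and the same assessments, and the section itself sets out to compensate the arms equally.

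A reader might go further in three ways that the document does not support.

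- **Counting the closing gifts.** The last session includes "Give blessings, encouragement, and gifts", and one could add this to the weekly goods. But Table 1 lists it as programme content, so it is part of the treatment being tested and is not part of this point.
- **Putting a number on the bias.** Suppose, as pure assumptions, loss of 15% in the ACT arm and 35% in the wait-list arm, with those lost differing from completers by 0.5 SD. A completers-only comparison would shift by (0.35 − 0.15) × 0.5 = 0.10 SD. Nothing in the protocol supports those rates, and the plan does not use a completers-only analysis. The sign is also open. If those lost are worse off, the control completers' mean improves by 0.35 × 0.5 = 0.175 SD and the ACT completers' mean by 0.15 × 0.5 = 0.075 SD, so the shift works against ACT. If those lost are better off, it favours ACT.
- **Saying that analysis cannot help at all.** That is too strong for drop-out, where the mixed models help under missing at random. It is fair only for goodwill.

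**Conclusion.** The point holds for the weekly goods alone. On the natural reading of Quality Control, an incentive meant to encourage completion is given up to eight times in the ACT arm and not at all in the wait-list arm before T1. The difference is avoidable, is not part of the ACT programme and does not follow from a wait-list design. It could cause unequal drop-out and, to a small and unquantifiable degree, more favourable patient-reported scores in the ACT arm. The direction and size of any net bias cannot be derived from the document.

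The conclusion assumes that the closing sentence of the section governs the wait-list arm's share of the goods. If the sponsor meant both arms to receive them weekly from the start, there is no imbalance, and only the wording needs correcting.

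**What to change.** Amend the last sentence of Quality Control so that wait-list patients receive the same goods on the same weekly schedule during their eight weeks of usual treatment. The protocol gives no weekly visit schedule for usual treatment. If no weekly contact is planned, give controls the same total before T1. In the preceding sentence, state that the reference to all patients means both arms.

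The cost is one sentence of amendment and earlier distribution of inexpensive items to 33 controls. If controls are also to be compensated during a later ACT course, a second set of items is needed. The Table 1 sessions need no change.
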